### Outcome measures

#### Medical history/assessment of concomitant medication and comorbidities

A medical history covering recorded previous illnesses (both psychiatric and somatic), past surgeries, allergies, intolerances, current and past medications, use of stimulants or addictive substances based on the participant’s statement, family and social history, as well as subjective side effects of previous tumor-specific treatments based on the participant’s statement and medical records will be obtained during the study visit.

#### Physical examination

A standardized neurological examination will be performed at the study visit, covering motor, sensory, cerebellar, cranial nerve, and language domains, with key deficits documented in predefined categories for subsequent analyses.

#### Karnofsky performance score

Trained clinicians will rate the Karnofsky Performance Status at the study visit using standardized anchor descriptions, and the timing of rating (before questionnaire review) will be prespecified to minimize observer bias.

#### MRI

MRIs are acquired as part of routine care and will be evaluated once for the purposes of this study. The study-specific analysis is conducted without knowledge of the questionnaire results. The MRI closest to the study visit (within a prespecified time window) will be used to code tumor location using predefined anatomical categories, and tumor extent will be operationalized using imaging-defined measures (e.g., contrast-enhancing core location and FLAIR hyperintensity involvement), with explicit rules for multilobar or multifocal disease.

*Patient-Reported Outcome Measures.* Table 1 gives an overview of the study endpoints and all measurement instruments used.

### Eligibility criteria

The following criteria apply for inclusion in the study: newly diagnosed glioblastoma, isocitrate dehydrogenase (IDH) wild-type (CNS WHO Classification 2021) after completion of primary radiotherapy and before first recurrence (local MRI assessment according to RANO 2.0 [27]), and an age of at least 18 years. Exclusion criteria include language barriers or clinically significant aphasia as assessed by the investigator, a known tumor predisposition syndrome such as Li-Fraumeni syndrome or Cowden syndrome, a history of other malignant tumors, and recurrent disease. Eligibility is assessed during a preliminary screening conducted by a board-certified physician with expertise in neuro-oncology as part of the routine outpatient consultation. Participants are recruited through neuro-oncology centers and departments in Germany. No financial compensation is provided for participating centers or patients. Likewise, insurance coverage for participants is not offered.

### Sample size calculation

A sample size calculation has been performed for a multiple linear regression analysis with ten candidate predictor domains: marital status (single, married, divorced, or widowed), age (in years), physical impairment (Karnofsky Performance Status), sex (male/female), depression (PHQ-8), anxiety (GAD-7), social support (SUCE−4), health-related quality of life (EORTC QLQ-C30 and EORTC QLQ-BN20), time since diagnosis (in days) and tumor location (brainstem, frontal, parietal, cerebellum, temporal, occipital, basal ganglia, or spinal). An exploratory sample size calculation was conducted for the planned multiple linear regression analysis, including approximately 20 regression parameters, accounting for the use of dummy coding for categorical variables with more than two levels. Based on a medium effect size assumption (f^2^ = 0.15; corresponding to R^2^ ≈ 0.13), an alpha level of 0.05, and a desired statistical power of 0.80, the required sample size was estimated at 157 participants using G*Power. This calculation should be interpreted as exploratory, particularly given the uncertainty regarding the magnitude of the expected effects and the possibility that effects may be smaller than anticipated. Therefore, all analyses will report confidence intervals and effect size estimates alongside significance tests to allow for an informed interpretation of the findings, irrespective of whether medium-sized effects are observed. To account for an anticipated attrition and data loss rate of approximately 15% (e.g., due to incomplete questionnaires, missing covariate data, or exclusions during data cleaning), the planned recruitment target was increased from 157 to 180 participants.

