### Study procedures

Patients can be included in the study after completion of primary radiotherapy and before the first recurrence (local MRI assessment according to RANO 2.0 [27]). After being informed about the study objectives during a physician consultation, patients provide written informed consent prior to enrolment. Questionnaires are completed independently by participants without the presence of relatives. During a single outpatient visit, trained staff perform a standardized clinical and neurological assessment, including Karnofsky Performance Status. Participants also complete the predefined self-report instruments listed in Table 1, which are administered under strictly standardized self-completion conditions. If, when completing the SSEV questionnaire, at least one question is answered with “less than once a week” or more often, further evaluation will be conducted during a medical consultation on the same day, and based on its results the patient will be referred to psycho-oncological care. Patient data are obtained from medical records by a clinical investigator based on a standardized case report form (demographics, diagnosis/tumor data, previous cancer treatment, MRI findings, medical history, medication, vegetative symptoms, substance use, family history of cancer) and the study visit. The recruitment period runs from March 18, 2026, through March 17, 2028. As the primary study center, Essen is expected to recruit approximately 60 participants, or 30 per year. The remaining approximately 120 participants in the planned total sample of approximately 180 participants, including anticipated dropouts, will be recruited across the other participating centers. Each center is expected to recruit approximately 10–20 participants over the two-year recruitment period. The regular follow-up of patients with glioblastoma at these specialized centers provides an established population from which potentially eligible participants can be screened. Based on these ongoing clinical follow-up structures and the multicenter design, recruitment of the planned study population by March 17, 2028, is considered feasible.

**Table 1 Tab1:** Overview of study endpoints

Endpoints	Measure	Brief description
*Primary*		

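### The recruitment target of 180 covers about 13% loss rather than the stated 15%: a minor inflation slip that leaves 153 analysable participants instead of 157

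*Protocol article*

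**What the plan says.** The Sample size calculation section sizes a multiple linear regression "including approximately 20 regression parameters", with a medium effect of f² = 0.15 (R² about 0.13), "an alpha level of 0.05" and "a desired statistical power of 0.80". On these inputs "the required sample size was estimated at 157 participants using G*Power".

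The section then allows for an "anticipated attrition and data loss rate of approximately 15" percent. Its examples are questionnaires not fully answered, covariates not recorded, and records removed in data cleaning. For this reason, "the planned recruitment target was increased from 157 to 180 participants".

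The Study procedures section confirms that 180 is the gross number. It speaks of a "planned total sample of approximately 180 participants, including anticipated dropouts".

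**The concern.** If 180 is the number recruited and 157 the number needed for analysis, the allowance works only if 157 remain after the stated loss. A loss rate is a fraction of those recruited, so the required number has to be divided by one minus that rate. The step from 157 to 180 does not match this for 15%; it is closer to an increase of 15% on 157.

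What is at stake is the consistency of a published figure. Taken at face value, the required number, the loss rate and the recruitment target do not quite fit together. A reader who relies on them would credit the study with slightly more protection against data loss than it has.

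**Working it through.** **Inputs, all from the Sample size calculation section:** f² = 0.15, alpha 0.05, target power 0.80, about 20 parameters, required N 157, loss about 15%, target 180.

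**Step 1: reproduce the plan's own figure.** The test is taken to be the omnibus F-test that R² = 0 in a fixed-effects linear regression with u parameters. Power is the probability that a noncentral F variable, with df1 = u, df2 = N − u − 1 and noncentrality λ = f² × N, exceeds the 95th percentile of the central F.

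With u = 20:

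- N = 156: power 0.7997.
- N = 157 (df2 = 136, λ = 0.15 × 157 = 23.55): power 0.8034.

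The smallest N with power of at least 0.80 is therefore 157, an exact match. The stated R² also agrees: 0.15 / 1.15 = 0.130.

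**Step 2: check the allowance for loss.**

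- Recruits needed to keep 157 after 15% loss: 157 / (1 − 0.15) = 184.7, so 185.
- Remaining from 180 after 15% loss: 180 × 0.85 = 153, which is 4 below 157.
- Largest loss at which 180 still keeps 157: 1 − 157/180 = 23/180 = 12.8%.
- For comparison, 157 × 1.15 = 180.55.

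**Step 3: effect on power.** At N = 153 with u = 20 (df2 = 132, λ = 0.15 × 153 = 22.95), power is 0.788. That is 1.2 percentage points below 0.80.

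**Step 4: sensitivity to the approximate inputs.**

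| Recruited | Loss | Analysed | Parameters | Power |
|---|---|---|---|---|
| 180 | none | 180 | 20 | 0.875 |
| 180 | 12.5% | 157 | 20 | 0.803 |
| 180 | 14% | 154 | 20 | 0.792 |
| 180 | 15% | 153 | 20 | 0.788 |
| 180 | 16% | 151 | 20 | 0.780 |
| 180 | 15% | 153 | 19 | 0.801 |
| 180 | 15% | 153 | 21 | 0.776 |

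Analysed numbers are rounded down to whole participants. One parameter more or fewer moves power by about as much as the inflation slip does.

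**The case against.** The case for leaving the sentence alone has four parts.

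1. **The inputs are approximate.** The protocol says approximately for the loss rate, the parameter count and, in Study procedures, the total. A covered loss of 12.8% is about two points from an approximate 15%. The listed predictors can be counted as 19: marital status 3, tumor location 7, one each for age, sex, Karnofsky status, PHQ-8, GAD-7, SUCE-4 and time since diagnosis, and 2 for quality of life if each EORTC instrument contributes one score. That last item is an assumption, because the section does not fix it. With 19 parameters, 153 participants give 0.801. This stands as a reason to call the slip minor. It does not remove it: the approximation runs both ways (21 parameters give 0.776), and the protocol's own 157 is the value for exactly 20.

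2. **Multiple imputation is planned.** The Statistical analyses section says that missing values will be imputed. Two of the three named sources of loss, incomplete questionnaires and missing covariates, would then not necessarily remove participants, and the effective loss could be below 15%. This is the strongest point, and it largely stands. But the sample size section counts those same sources as loss and inflates for them, so its arithmetic should be right on its own terms. Imputation also does not restore full information or recover records excluded in cleaning.

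3. **The calculation is exploratory.** The protocol says so of both the calculation and the analyses. It plans ridge regression, and generalized models if the outcome is skewed or zero-inflated, and it does not name the omnibus F-test as a decision criterion. A gap of 1.2 points changes no stated decision. This stands as to consequence, but a correct statement of the margin costs nothing.

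4. **The origin of 180 is not stated.** A reader might infer that 15% was simply added to 157. The documents do not say so. The product is 180.55, which rounds up to 181, so a convenient round number is also possible. The finding does not depend on which it was.

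**Conclusion.** The point holds as a minor slip. A 15% loss from 180 leaves 153, not 157; the strict requirement is 185 recruits, and 180 covers a loss of about 12.8%. The cost in power is about 0.79 against the stated 0.80. That figure rests on the omnibus F-test, exactly 20 parameters, f² = 0.15 and a full 15% of recruits dropping out of the analysis.

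A reader might go further and infer that the study is underpowered, or that its stated figures are irreconcilable. The documents do not support this. The relevant inputs are given as approximate, the planned imputation may keep the analysed number above 153, and the gap lies within what one parameter more or fewer would produce. The required number itself, 157, is correct.

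**What to change.** Keep the target of 180 and correct the sentence in the Sample size calculation section. Either of these would do:

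- 'A recruitment target of 180 allows for a loss of about 13% while retaining 157 analysable participants.'
- 'With a loss of 15%, 180 recruits leave 153 analysable participants, which gives a power of about 0.79.'

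The cost is one sentence. No additional enrolment is needed. The predictor set should stay as it is: merging tumor-location categories to bring the requirement down to 153 would alter a prespecified predictor for a trivial gap, and it would assume a count of exactly 20 that the protocol does not claim.

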#### Statistical analyses

Associations between suicidality and candidate predictors will be examined using regression models appropriate to the distribution of the SSEV outcome, defined as the continuous 6-item SSEV composite score assessing suicidal ideation during the past four weeks. Depending on distributional properties, linear regression models will be used for approximately continuous and symmetric outcomes, while generalized models will be considered in case of marked skewness or zero inflation. All assumptions (including linearity, homoscedasticity, and distribution of residuals) will be assessed and reported where applicable. Prior to multivariable modeling, descriptive statistics and bivariate correlations (Pearson or Spearman, depending on scale properties and distribution) will be computed to describe the data structure. These analyses are purely exploratory and will not be used for variable selection. Multicollinearity will be assessed using variance inflation factors (VIF).

As secondary and sensitivity analyses, additional models will be fitted using (a) a dichotomized suicidal ideation outcome (presence vs. absence of suicidal ideation, defined as a 6-item SSEV score ≥ 1) and (b) lifetime suicide attempts assessed by the dedicated dichotomous SSEV item. These analyses will include the same set of predictors and are intended to assess the robustness of findings across alternative operationalizations of suicidality. All analyses are considered exploratory and hypothesis-generating and are not intended to establish causal relationships.

Given the exploratory nature of the study, all prespecified candidate predictors will be entered simultaneously into a multivariable model without prior univariable screening. To reduce overfitting and improve the stability of estimates in the presence of a relatively high number of predictors, penalized regression (ridge regression with tuning via cross-validation) will be applied. Model performance will be internally validated using bootstrap resampling (e.g., 5,000 resamples) to estimate and correct for optimism in performance metrics. Regression coefficients with 95% confidence intervals will be reported, along with model performance measures such as R^2^ and root mean squared error (RMSE) for the continuous outcome.

Missing data will be reported for all variables. Missingness patterns will be explored descriptively, and multiple imputation will be used to handle missing values under the “missing at random” (MAR) assumption. All predictors included in the analysis model will also be included in the imputation model.

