### Study design

Approval for this prospective, multicenter observational study was granted by the Ethics Committee in Essen, Germany (approval no. 25—12,746-BO), and all participating sites obtained local ethical approval before enrolling participants. The study will recruit 180 patients diagnosed with glioblastoma. Manuscript preparation followed the STROBE (Strengthening the Reporting of Observational Studies in Epidemiology) reporting guidelines. To ensure feasibility and reduce burden on participants, all assessments are scheduled within one outpatient visit. The study is conducted in accordance with the Declaration of Helsinki and applicable national legislation.

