Suicidality	Scale for Suicidal Experience and Behavior (SSEV) [28]	The SSEV is a 9-item self-report questionnaire assessing suicidal thoughts, impulses, intentions, plans, and attempts within the past four weeks. The primary outcome will be a continuous composite score based on the first six items (range 0–18), with higher scores reflecting greater suicidal ideation severity. The 6-item score was selected to ensure a standardized and sensitive measure across participants Secondary and sensitivity analyses will include a dichotomized version of suicidal ideation (score ≥1 on the 6-item scale, indicating presence vs. absence). Lifetime suicide attempts will be assessed separately using a single yes/no item and treated as a secondary outcome
*Secondary*		
Depressive symptoms	Patient Health Questionnaire−8 (PHQ-8) [30]	Depressive symptoms are measured by the validated German PHQ-8, with responses on a 0–3 Likert scale (“0-not at all” to “3-nearly every day”). Scores will be analyzed continuously and categorized into standard severity levels (minimal to severe). The PHQ-8 was preferred over the PHQ-9 to avoid inclusion of a suicidality item and thus prevent overlap with outcome measures in suicidality analyses
Anxiety symptoms	Generalized Anxiety Disorder-7 (GAD-7) [31]	Anxiety is assessed using the GAD-7, with standard response options from 0 (“not at all”) to 3 (“nearly every day”) and established cutoffs for mild (≥ 5), moderate (≥ 10), and severe (≥ 15) anxiety
Health-related quality of life (disease-specific)	EORTC QLQ-C30 [32] and EORTC QLQ-BN20 [33]	Quality of life is assessed using the EORTC QLQ-C30, a 30-item instrument evaluating general cancer-related quality of life. In addition, the EORTC QLQ-BN20 is used to capture brain tumor–specific symptoms and functional impairments, including visual problems, communication difficulties, future uncertainty and motor dysfunction
Social support	Short Questionnaire on Social Support in Chronic Illness (SUCE−4) [29]	The SUCE−4 is a brief instrument assessing perceived social support in individuals with chronic illness. All four items are assessed on a 5-point Likert scale and coded numerically (0 to 4 from ‘no’ to ‘yes’), with any assistance during completion and any missing items documented according to prespecified rules. The “social support” score ranges from 0 to 16 and is the sum of all four items

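### Lifetime suicide attempts have no time bound, so a model of them cannot serve as a robustness check on suicidal ideation in the past four weeks

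*Protocol article*

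**What the plan says.** The Statistical analyses section takes as its outcome the SSEV score "defined as the continuous 6-item SSEV composite score assessing suicidal ideation during the past four weeks". It then plans two further models, described jointly as secondary and sensitivity analyses: (a) the same six-item score dichotomised at 1 or more, and (b) "lifetime suicide attempts assessed by the dedicated dichotomous SSEV item". One sentence gives both the same role: "These analyses will include the same set of predictors and are intended to assess the robustness of findings across alternative operationalizations of suicidality".

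Table 1 treats the item differently: "Lifetime suicide attempts will be assessed separately using a single yes/no item and treated as a secondary outcome". There it stands as an outcome in its own right, with no mention of robustness.

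The predictors are listed under Sample size calculation: "A sample size calculation has been performed for a multiple linear regression analysis with ten candidate predictor domains". The domains are marital status, age, Karnofsky status, sex, PHQ-8, GAD-7, SUCE-4, QLQ-C30/BN20, time since diagnosis and tumor location, coded in about 20 regression parameters. On timing, Study design says that "all assessments are scheduled within one outpatient visit", and Study procedures says "Patients can be included in the study after completion of primary radiotherapy and before the first recurrence".

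**The concern.** A sensitivity analysis is informative when it aims at the same quantity as the primary analysis and changes one assumption or one coding choice. Model (a) does this: it keeps the four-week window and changes only the scale. Model (b) changes both the event and the window. It counts any attempt at any time in the patient's life, and nothing in the article limits it to attempts after diagnosis.

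The plan does not allow for this when it comes to interpretation. If the attempt model agrees with the primary model, the finding will be reported as holding across definitions of suicidality. If it disagrees, the finding will be reported as fragile. Neither conclusion follows. The study is meant to inform screening and referral pathways, so a mistaken statement about robustness would carry some weight with readers. The Perspective section itself faults earlier work for mixing definitions and observation windows, and model (b) brings that mixture into this study's own check.

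**Working it through.** **1. The two outcomes side by side**

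| | Primary outcome and model (a) | Model (b) |
|---|---|---|
| Event | Ideation, six-item SSEV score | Suicide attempt, one yes/no item |
| Window | Past four weeks | Lifetime, no lower bound |
| Can predate the tumor? | No, the visit follows radiotherapy | Yes |

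**2. The predictors against an attempt made before the tumor**

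- Time since diagnosis and tumor location did not yet exist as exposures.
- Karnofsky status, PHQ-8, GAD-7, SUCE-4 and QLQ-C30/BN20 describe the patient around a visit after radiotherapy, so they come after the attempt. An association could reflect a stable vulnerability, or the earlier attempt predicting today's symptoms.
- Sex is unaffected, age is not a post-diagnosis state, and marital status may or may not have come first. The mismatch therefore affects most of the predictors, but not all.

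**3. How far the two coefficients can differ (illustration with assumed inputs)**

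Model, with 200,000 simulated patients:
- current depression d and trait vulnerability t are standard normal with correlation 0 or 0.5;
- current ideation: logit = -1.7 + 1.0 d;
- an attempt after diagnosis: logit = -3.2 + 1.0 d;
- an attempt before diagnosis: logit = -3.2 + 1.0 t.

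Attempt prevalence comes out at about 6%. The fitted ideation log odds ratio for d is 1.0 in every row (1.00-1.01). The attempt log odds ratio for d is:

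| Assumed share predating diagnosis | Trait correlation 0 | Trait correlation 0.5 |
|---|---|---|
| 0% | 1.00 | 1.00 |
| 50% | 0.46 | 0.72 |
| 90% | 0.07 | 0.54 |
| 100% | 0.01 | 0.49 |

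The ideation association never changes, yet the attempt coefficient runs from 0.01 to 1.00. It depends on two things that the article does not plan to measure: when the attempt happened and how stable the vulnerability is.

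**4. Expected number of events**

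The plan's own figure first. With f² = 0.15, 20 parameters, alpha 0.05 and power 0.80, the noncentral F calculation gives N = 157 (power 0.803), matching the article. So about 20 parameters is indeed the model size intended.

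The recruitment target is 180. After the stated 15% loss, 180 × 0.85 = 153. The article gives no attempt rate, so the rates below are assumptions. Events = N × rate; events per parameter = events / 20.

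| Assumed rate | Events, N = 153 | Events, N = 180 | Events per parameter |
|---|---|---|---|
| 2% | 3.1 | 3.6 | 0.15-0.18 |
| 5% | 7.7 | 9.0 | 0.38-0.45 |
| 10% | 15.3 | 18.0 | 0.77-0.90 |

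Even at 10% there is less than one event per parameter.

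**5. What this means for the planned ridge fit**

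The section plans ridge regression tuned by cross-validation and bootstrap validation with, for example, 5,000 resamples. With 3 events among 153 patients, the chance that a resample contains none is (150/153)^153 ≈ 0.048, or about 240 of 5,000. If tuning used ten folds (an illustrative choice, not stated in the article), at least seven would contain no event. Coefficients would exist, but the penalty would largely determine them.

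**The case against.** The strongest reply is that the study claims very little. The article states: "All analyses are considered exploratory and hypothesis-generating and are not intended to establish causal relationships". Past attempts and current depression can be associated through stable vulnerability; the simulation gives 0.49 even when every attempt predates diagnosis and the trait correlation is 0.5. Table 1 makes lifetime attempts a legitimate secondary outcome, and modelling a secondary outcome is no fault. All of this stands. It does not rescue the robustness role, because the difficulty is that the two outcomes are not comparable, and a disclaimer about causality does not address that.

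It might also be said that Table 1 introduces the SSEV as covering the past four weeks, attempts included. But the item used in model (b) is called a lifetime item both there and in the Statistical analyses section.

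Four stronger readings are tempting, and the document does not support them:

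- A reader might infer that model (b) cannot be estimated. That would apply to an unpenalised logistic fit. The ridge sentence is not confined to the primary outcome, and ridge returns finite coefficients. What remains is imprecision and dependence on the penalty.
- A reader might apply the 21.5% quoted in the Introduction to model (a) and put a ceiling of about 33 on its events. That figure comes from a cohort with mixed intracranial tumors and counts thoughts reported at least once during follow-up. It is no ceiling for a score of 1 or more on six SSEV items.
- A reader might conclude that the primary model wrongly omits prior attempts. That is a modelling preference, and it sits badly with the expectation of only a handful of positive patients.
- A reader might say that attempts can precede every predictor. Sex, age and possibly marital status are exceptions.

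**Conclusion.** The point holds in a limited form. The article gives model (b) a purpose that it cannot serve: an outcome without a time bound, set against mostly current or disease-defined predictors, does not test findings about four-week ideation. This follows from the text alone and needs no assumed rate.

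The sizes are illustrative. The range of 0.01 to 1.00 for the attempt coefficient rests on the assumed simulation inputs, and the 3-9 expected events on an assumed rate of 2-5%. The share of attempts that predate the tumor is unknown.

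The reach is narrow. The primary analysis, the sample size and model (a) are untouched, and lifetime attempts remain a valid secondary outcome. What is wrong as written is the robustness claim attached to them.

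**What to change.** In the Statistical analyses section, limit the robustness sentence to (a), the dichotomised four-week score. Keep lifetime attempts as the separate secondary outcome that Table 1 already describes, and report them as n, % and exact 95% CI. If a model for them is still wanted, label it exploratory, state that it is not a robustness check of the primary result, and report the number of events beside it.

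The cost is a change of wording before the data are analysed. One sparse exploratory model loses its robustness role. No data collection, sample size or primary analysis changes.
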